#### Missing data

Patterns of missing data (due to mortality and otherwise) will be analyzed. If the missing appears relatively random, multiple imputation will be used; otherwise, missingness will be addressed through last observation carried forward (LOCF). Imputed results will be compared to non-imputed results. A secondary analysis for all primary and secondary outcomes will be to test for dependence (through interactions) between treatment and time.

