### Sample size

The sample size was determined by the amount of philanthropic funding we secured for the Trial which was sufficient to provide $12,000/year to 100 participants. After accounting for anticipated attrition we determined that a 250 person sample was needed – 100 in the intervention group and 150 in the control group (overrecruited for differential attrition). We conducted power analyses based on the literature and pilot study findings to determine detectable treatment effects in the primary outcomes of interest. Power analyses methods and results for each primary outcome are described below. Recruitments sites were selected for serving racially diverse, low-income patient populations. Our pilot study sample was 50% Black, 35% white, 4% Asian, 4% mixed, and 7% other. 52% of the sample identified as Hispanic or Latino.

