### Allocation

Each week participants with completed baseline surveys in Qualtrics will be randomly assigned to one of the study conditions using a computer generated 1:1.5 randomization schedule stratified by age and recruitment site. We will over recruit for the control arm to compensate for an expected 30% differential attrition rate (an estimate derived from yet unpublished U.S. guaranteed income RCTs). Randomization schedule will be stored in a password protected excel spreadsheet that can only be accessed by the principal investigator and senior research coordinator who are not involved in the day-to-day recruitment of participants.

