#### Power analysis for primary outcomes

All power calculations were conducted in Power Analysis and Sample Size (PASS) 2023. Power was calculated at alpha=0.05 with 200 patients at five timepoints. For all power estimates, we assumed an 8% mortality rate between primary timepoints; therefore, 28% of patients will be deceased by the 12 month time point (American Cancer Society, 2019). Power calculations were conducted with missing timepoints rather than on imputed data since we plan to compare imputed to non-imputed models. We further assumed an exchangeable correlation structure with a moderately strong intraclass correlation (r = 0.6).

Many estimates were obtained through the pilot analysis. We conducted an observational, pre-test/post-test pilot study in which we recruited 150 financially burdened cancer patients and provided them with a one-time grant of $1,000. We measured primary and secondary outcomes of interest prior to the intervention delivery and two months after to examine changes over time. We expect that the full trial, which will provide participants with 12 times the amount of cash that was provided in pilot, will yield higher treatment effects. We believe the estimates from the pilot are conservative estimates for the full trial, and any estimates not obtained from the pilot were overly conservative to ensure full power.

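### The missing-data rule turns to LOCF when missingness looks non-random and fills in outcomes after death; it can create or mask a between-arm difference

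*Protocol article*

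**What the plan says.** The Missing data section opens with "Patterns of missing data (due to mortality and otherwise) will be analyzed", so deaths and other losses are grouped together. One rule then follows for both: "If the missing appears relatively random, multiple imputation will be used; otherwise, missingness will be addressed through last observation carried forward (LOCF". It gives no criterion for judging randomness and no separate handling of death. The section adds "Imputed results will be compared to non-imputed results" without saying which set of results is primary.

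Two other sections show how much data the rule would govern. Power analysis for primary outcomes states: "we assumed an 8% mortality rate between primary timepoints; therefore, 28% of patients will be deceased by the 12 month time point". This is one overall rate, not split by arm. Allocation states: "We will over recruit for the control arm to compensate for an expected 30% differential attrition rate". Whether the 30% means percentage points or a relative excess is not said. Sample size gives "100 in the intervention group and 150 in the control group (overrecruited for differential attrition". Statistical methods names linear mixed models for continuous outcomes and GEE for binary ones, using all five time points.

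**The concern.** There are three faults in the rule as written.

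- **The switch.** Observed data cannot separate missing at random from missing not at random. Dropout that differs by arm or by measured covariates may look far from random and still be missing at random, in which case multiple imputation or a likelihood-based mixed model handles it. The rule would move such data to LOCF, which assumes that each patient stays at the last recorded value.
- **Death.** Financial toxicity, quality of life and missed appointments are not defined after death. Under either branch the rule supplies values for people who have died. This fault needs no assumption about trends or differential dropout.
- **Differential attrition.** Recruiting more controls restores numbers but not comparability. If controls leave more often, more of their values are frozen at earlier visits. Any change over time shared by both arms then appears as a difference between them.

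At stake are the comparisons on all three primary outcomes.

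**Working it through.** **Inputs from the protocol article.** Deaths 8% per 3-month interval; 100 intervention and 150 control patients; 30% differential attrition; COST SD 7.1, pilot difference 2.4, intraclass correlation 0.6.

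**Assumptions.** Deaths equal in both arms. The 30% is read as 30 points of extra control dropout over 12 months, spread evenly. Both arms share a linear change D over 12 months. There is no treatment effect and dropout is unrelated to outcome. The documents give no trajectory for any outcome. Their only COST change over time is the 2.4 points of the pre/post pilot, and that followed a $1,000 grant.

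**1. The plan's own figure.** 1 − 0.92⁴ = 0.284, which reproduces the stated 28%. That is about 71 of 250 patients.

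**2. Assessments after death.** Expected number = 250 × Σ(1 − 0.92ᵏ), k = 1 to 4 = 250 × (0.080 + 0.154 + 0.221 + 0.284) = 185. Planned post-baseline assessments = 250 × 4 = 1,000, so about 18% fall after death.

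**3. Month-12 values missing.** Intervention 28%. Control 1 − 0.716 × 0.70 = 50%.

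**4. LOCF difference at month 12.** With probability s of remaining from one visit to the next, LOCF retains on average (s + s² + s³ + s⁴)/4 of the change D.

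- Intervention: s = 0.92, retained 0.815.
- Control: s = 0.92 × 0.70^(1/4) = 0.8415, retained 0.662.
- Spurious difference: (0.815 − 0.662) × D ≈ 0.154 × D. With 10% v 40% dropout it is 0.159 × D.

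Averaged over the four follow-up visits the factor is 0.531 − 0.449 = 0.082.

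**5. Size and false-positive rate.** Simulation of 8,000 null trials per setting, 100 v 150 patients, SD 7.1, correlation 0.6, two-sided 0.05, no covariates:

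| D (COST points) | Month-12 difference | Rejections | Visit-averaged difference | Rejections |
|---|---|---|---|---|
| 0 | 0 | 5% | 0 | 5% |
| 2.4 | 0.38 | 7% | 0.21 | 5% |
| 5 | 0.77 | 13% | 0.41 | 8% |

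Testing change from baseline instead gives somewhat higher rejection: at month 12, about 7% at D = 2.4 and 16% at D = 5. With the same dropout and only observed month-12 values, the difference is about zero and rejection stays near 5%.

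**6. If the 30% is relative.** For example, 20% v 26% dropout gives (0.715 − 0.683) × D ≈ 0.03 × D, or 0.08 points at D = 2.4.

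**7. Dilution of a real effect.** Suppose the intervention arm rises linearly to 2.4 and control stays flat. With deaths alone, LOCF gives 2.4 × 0.815 = 1.96. With 10% dropout in that arm as well, it gives 2.4 × 0.766 = 1.84.

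**The case against.** A reader might infer that the protocol's own death and attrition rates are enough to produce a false treatment difference. The documents do not support that. The death rate is a single figure, and equal death rates contribute no spurious difference. Differential attrition biases LOCF only if outcomes drift over time or dropout depends on outcome, and no such pattern is documented. A 5-point drift is an assumption; near the documented 2.4 the effect on error rates is small.

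The month-12 contrast is also not the named analysis. The plan uses all five time points and leaves the treatment-by-time interaction to a secondary analysis. Averaging over visits roughly halves the distortion.

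Nor can one say that the LOCF branch is the likely one: with no criterion stated, dropout that differs only by arm might be judged random enough for multiple imputation. It would likewise be too strong to say that the unimputed GEE needs dropout completely at random, since an adjusted GEE tolerates dropout explained by arm and the included covariates.

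Finally, the comparison with non-imputed results is a real mitigation, and the Retention section plans repeated contact and a higher incentive if response in an arm falls to 75%. All of this stands and limits the size of the problem. It does not rescue the rule: with no analysis named primary, a disagreement would be settled after the results are seen, and better retention does nothing about values imputed after death.

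**Conclusion.** The rule is wrong as written and should be replaced. Two faults hold without further assumptions: LOCF is selected on a judgement the data cannot settle, in the case where it has least justification; and outcomes are filled in for patients who have died. The bias between arms is conditional. Its sign follows D: it favours the intervention if COST improves in both arms and control if it declines in both. Its size depends on D, on reading the 30% as percentage points and on using the month-12 contrast; under those assumptions it is about 0.15 × D. At D = 2.4 this is about 15% of the pilot difference. Attenuation of a true effect is an equally real consequence.

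**What to change.** Delete LOCF and the switch on apparent randomness. In their place:

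- **Continuous outcomes:** name the already planned non-imputed, likelihood-based mixed model, on values observed while alive, as the primary analysis.
- **Death:** impute nothing after death, and report deaths by arm beside the outcome results.
- **Binary outcomes:** use multiple imputation of gaps before death, with arm and earlier outcomes in the imputation model, or weighted GEE.
- **Sensitivity to non-random dropout:** use delta-adjusted (pattern-mixture) multiple imputation. A composite analysis that counts death is optional.
- **Attrition assumption:** state whether the 30% is in percentage points or relative.

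The cost is revised wording and some extra programming, with no new data. Intervals may be slightly wider than under LOCF.

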### Data monitoring

The PI will conduct monthly quality assurance and data integrity checks which will include checking a random set of cases in the database to ensure that key data points are available.

## Discussion

Over the last 50 years UCT demonstration projects conducted across the globe have generated a compelling body of evidence that demonstrates positive impacts on a range of health-related outcomes. UCT recipients in the US and Canada experienced improvements in birth outcomes, (Kehrer and Wolin, 1979; Chung et al., 2016) education attainment, (Maynard and Murnane, 1979; Forget, 2011) psychiatric conditions and substance abuse disorders (Costello, 2010). Globally, UCT has produced large, clinically significant reductions illness, injury, psychiatric emergencies, and related healthcare utilization (Forget, 2011, 2013; Baird et al., 2014). While other studies have demonstrated the positive health effects of UCT in other low-income populations, this trial will examine the benefit of providing ongoing income support to people with serious illnesses like cancer. Financial anxiety among cancer patients is high, but appropriate, given that 42.4 percent of U.S. cancer patients deplete their entire life's assets within two years of diagnosis (Gilligan et al., 2018). In low-income populations, income loss is a significant driver of financial toxicity, which is associated with an array of adverse health and treatment outcomes (Yabroff et al., 2018). Paid sick leave, medical leave under the Family Medical Leave Act (FMLA), and reasonable accommodations under the Americans with Disabilities Act (ADA) improve job retention in cancer patients (Blinder and Gany, 2020). However, these employment protections are either not accessible to all workers or are structured in a way that disadvantages low-wage workers (Vohra-Gupta et al., 2021). For example, just 33 percent of low-wage workers in the U.S. have any paid sick leave, compared to 95 percent of the highest paid workers (United States Bureau of Labor Statistics, 2022).

The absence of a strong social safety net in the US, relative to those of similarly developed nations, leaves many people at risk of health-related poverty (Liao et al., 2022). The consequences of poverty for individuals and society are well known, however, there are many barriers to the implementation of robust anti-poverty interventions in the U.S (Skidmore, 2018), Scientific evidence for the feasibility and effectiveness of UCT is growing, and so is bipartisan interest in guaranteed income as a cost-effective anti-poverty program (Ito, 2018). The appeal of our model is that it sidesteps one of the foremost ideological barriers to UCT: labor market participation. Although the labor market effects of UCT have been found to be negligible to positive, some are concerned that a guaranteed income would dissuade people from seeking employment (Hasdell, 2020). This study targets a population of people with serious illness, whom most people would agree should not have to work, and their family caregivers, who are engaging in the demanding work of providing care to a loved one. The US already has one federal program designed to protect income during illness and disability: Social Security Disability Insurance and Supplemental Security Income. It is well recognized that the current benefit from these programs is too low and that many recipients remain trapped in a cycle of poverty (Stapleton et al., 2006). Findings from GIFT may be directly applied to ongoing efforts to modernize disability income protections in the US. GIFT findings may have implications for non-governmental or market-based intervention as well. Health insurers and managed care organizations are interested in investing in the social needs of their beneficiaries, especially if they can demonstrate a return on investment relative to healthcare utilization and spending (Shrank et al., 2018).

The proposed study is an early effectiveness trial of UCT for cancer patients who have low incomes. Despite its many strengths there are some limitations that should be acknowledged. First, in order to verify patients' low-income status, we use Medicaid beneficiary status as a proxy variable for eligibility. As a result, this sample will not include low- to moderately low-income patients who may be experiencing financial hardship but do not have Pennsylvania Medicaid. Future studies of UCT for cancer may focus on recruiting participants with incomes slightly above the threshold for Medicaid. Second, this study relies predominantly on participants' self-reported survey data which may be limited by participant bias. In a supplemental mixed methods study, we plan to enhance GIFT trial findings by using participants' Medicaid claims data to analyze the impact of UCTs on healthcare utilization and spending and explore underlying mechanisms with qualitative interviews. Similarly, the GIFT trial will not examine the effect of UCT on caregivers, caregiver-patient dyads, or families. We may add a supplement to study these effects but have not yet developed these aims. Lastly, we are aware that what constitutes a clinically meaningful change in COST score has not been determined and that the measure has not been validated in low-income, racially diverse cancer patients. The principal investigator is currently conducting a study that aims to adapt, validate, and determine the predictive power of COST on clinical outcomes in a sample of low-income patients receiving care in a minority serving institution. These findings will aid in interpreting financial toxicity findings from the GIFT trial.

## Ethics statement

This protocol and the template informed consent forms have been approved by the University of Pennsylvania. Research assistants trained in human subjects research and the responsible conduct of research will receive additional training from the PI on the process for obtaining informed consent from participants. Informed consent forms have been audited for readability at the 6^th^ grade level. Participants will receive an information sheet and paper copy of the informed consent document for their records.
